**Statement**

Artemisinin-based combination therapies (ACTs) have recently been adopted by National Malaria Control Programmes in Africa as first line therapies to treat uncomplicated malaria, but the optimal choice of ACT remains uncertain. . Dihydroartemisinin-piperaquine (DP) is a promising candidate for first-line therapy of malaria. Preliminary results of pharmacokinetic studies indicate that the disposition of piperaquine is altered in children and this fact may affect the efficacy of the treatment. This project will evaluate the efficacy and the pharmacokinetics of DP in order to design a “best regimen” for the treatment of malaria in children.

**BACKGROUND**

Malaria endemic countries are facing the challenge posed by the wide spread of drug resistance[1, 2], which requires the implementation of alternative therapies.

Combination therapies, particularly ACTs, are advocated as the best way to improve drug efficacy while slowing the extension of the resistance. [3, 4]

Many countries in Africa[5-7], including Burkina Faso, have moved to artemether-lumefantrine (Coartem®, AL) or Artesunate/amodiaquine (AS/AQ) as first-line or second line in the treatment of malaria in a number of other countries [8]. In recent studies in Bobo-Dioulasso, Burkina Faso [5-7, 9], the efficacy against uncomplicated malaria of AL, considering both recrudescent and new infections after therapy, was significantly worse than that of DP (Zongo, et al., submitted). DP has also shown promising results in studies in Asia and Africa [10, 11] . However, DP has not been as extensively studied as other ACTs, and our understanding of its pharmacokinetics are incomplete. Indeed, this drug appears to have modified kinetics in infants and adults [12] which may seriously reduce its efficacy.

Therefore, we aim to study the pharmacokinetics properties of DP in children to provide evidence based data to allow optimal treatment of uncomplicated falciparum malaria in children.

**Goal**

To evaluate the efficacy and pharmacokinetics of DP for designing an optimal regimen for its use in children.

**Objectives**

1. To characterize the pharmacokinetics of piperaquine in children
2. To determine the efficacy and safety of DP for the treatment of uncomplicated falciparum malaria in Burkina Faso.
3. To search for associations between DP treatment outcomes and pharmacokinetics in individual patients.

**Study design**

1. Treatment efficacy

This will be an open-label trial in Bobo-Dioulasso, designed in accordance with WHO guidelines[13]. The target populations include residents of the catchments areas of the Colsama, Sarfalao, and Ouezzin-ville dispensaries in Bobo-Dioulasso. Children who present to the study clinics with symptoms suggestive of malaria will be screened with a thick blood smear. Subjects who meet selection criteria of treatment efficacy will be treated and followed up for 42 days. Efficacy outcomes will be assessed based on the 2006 WHO outcomes classification system [13].

2. Pharmacokinetic analysis

Pharmacokinetic assays and analysis will be performed at the Wellcome Trust Laboratory in Bangkok in collaboration with one of our staff in Bobo-Dioulasso and at UCSF.

Population kinetic studies using sparse sampling and capillary sampling are proposed to determine if the dosing of DP needs to be modified in young children. Sparse capillary sampling at day 0, 2 (2 hrs post dose), 4, 5, 7, 14, 21, 28, 35, 42 will be used to describe the kinetics of piperaquine. The sampling method is critical: capillary blood (200 µL) will be taken and plasma separated (centrifugation at 3000 g for 10 mn) and frozen at -20C. The assays and the analysis will be performed by the pharmacology laboratory in Bangkok ([name] and [name]). The exact time for sampling will be randomly allocated and scattered within the days indicated above. The clock hour at the time of sampling and dosing must be recorded accurately. It is important that the blood is obtained without squeezing the finger tip, as this will dilute the blood in interstitial fluids. Also important is to avoid any hemolysis, as this will interfere with the assay.

*3. Study outcome*

Primary outcome

- PK parameters: Piperaquine concentration-time profiles will be analyzed using non-linear mixed effects modeling as implemented in NONMEM. Different compartmental models will be tried and primary pharmacokinetic parameters will be parameterized as oral clearance (CL/F), steady state volume of distribution(s) (Vss/F), inter-compartment clearance(s) (Q/F) and absorption rate (ka). Continuous and dichotomy co-variates will be investigated. Exposure-response correlations will be investigated in case of recrudescence and/or reinfection in a significant number of patients.

Secondary outcomes

- Risk of recurrent malaria
- Risk of clinical and parasitological treatment failure

Risks will be estimated using the Kaplan-Meier product limit formula based on a modified intention-to-treat analysis.

- Prevalence of fever (defined as both subjective fever in the previous 24 hours and measured axillary temperature > 37.5C) on follow-up days 1, 2, and 3.
- Prevalence of parasitemia on follow-up days 2 and 3.
- Change in mean hemoglobin from day 0 to 42 (or day of rescue therapy for patients classified as LCF or LPF)
- Prevalence of gametocytemia on follow-up days 2, 3, 7, 14, 21 and 28.
- Change in the prevalence of molecular markers possibly associated with drug resistance on day 0 or the day of recurrent parasitemia, including polymorphisms in pfcrt and pfmdr1.
- In vitro sensitivity to antimalarial drugs.

Classification of treatment outcome

Response to treatment will be classified according to the 2006 WHO classification system with slight modifications[13] and will include adequate clinical and parasitological response (ACPR), early treatment failure (ETF), late clinical failure (LCF), and late parasitological failure (LPF)

For purposes of data reporting in the final analysis, treatment outcomes will be dichotomized based on the following definitions:

- Recurrent malaria = ETF + LCF
- Recurrent parasitemia = ETF + LCF + LPF.

All ETFs will be considered true treatment failures. For all LCFs and LPFs, molecular genotyping (based on polymorphisms in msp-1 and msp-2) will be used to distinguish recrudescence from new infection.

- Clinical treatment failure = All ETFs + LCFs due to recrudescence
- Parasitological treatment failure = All ETFs+LCFs+LPFs due to recrudescence

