# Follow up and laboratory procedures

## *1. Follow-up schedule*

Children will be asked to return to the clinic for follow-up on days 1, 2, 3, 4 , 5, 7, 14, 21, 28, 35, 42 and any unscheduled day that they feel ill. All patients will be reimbursed the cost of their transport to and from the clinic. At enrollment, details about the location of the patient’s residence will be obtained and if a subject does not return for a scheduled clinic follow-up appointment, the study personnel shall visit them at home. Patients who return on day 1 and fail to fulfill the criteria of *P. falciparum* mono-infection with a parasite density of 2000-200,000 parasites/ul will be excluded from the study and referred to the dispensary staff for management. At each repeat visit, temperature will be measured and a focused physical examination will be performed. A finger prick blood sample will be obtained on days 2, 3,4, 5, 7, 14, 21, 28, 35, 42 and any extra day they present with a fever to repeat thick blood smears and to save blood on filter paper. Hemoglobin will be re-evaluated on day 42 or at the time of clinical treatment failure (ETF or LCF).

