***4. Statistical analysis and sample size***

We will search for associations between diminished drug levels of piperaquine and clinical outcomes. Available resources will allow us to study 300 patients who complete study follow-up. Estimating a 10% loss to follow-up over 42 days, we will enroll 330 patients of whom 200 will have age range from 2 to 10 years. In our recent study at the same sites, the unadjusted 42 day risk of treatment failure with DP was 7.5%. Unadjusted failures are relevant in this analysis, as low levels of piperaquine may be associated with either recrudescence or new infections emerging during the elimination phase of piperaquine. It is estimated, based on our recent study that studying 300 patients will identify 22 unadjusted treatment failures. This sample size will provide the power to identify a 3-fold difference in unadjusted treatment efficacy between the lowest piperaquine level quartile and the remainder of subjects.

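### The hemoglobin outcome and the visit schedule name different failure classes, so late parasitological failures found before day 42 have no scheduled rescue-day hemoglobin

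*Protocol*

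**What the plan says.** Two sections of the protocol bear on this.

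- **Study design, Study outcome (secondary outcomes).** The outcome is "Change in mean hemoglobin from day 0 to 42 (or day of rescue therapy for patients classified as LCF or LPF"). ETF is not named.
- **Follow-up schedule.** The measurement rule is "Hemoglobin will be re-evaluated on day 42 or at the time of clinical treatment failure (ETF or LCF"). LPF is not named. The same section gives the purpose of the follow-up fingerpricks as "to repeat thick blood smears and to save blood on filter paper", with no mention of hemoglobin.

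The protocol keeps LPF apart from clinical failure in its classification of outcomes: "Recurrent parasitemia = ETF + LCF + LPF", whereas "Clinical treatment failure = All ETFs + LCFs due to recrudescence". On numbers, the sample-size section says "the unadjusted 42 day risk of treatment failure with DP was 7.5" per cent, and that "studying 300 patients will identify 22 unadjusted treatment failures".

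**The concern.** An outcome definition and the schedule that feeds it must ask for the same reading in the same children. Here they do not. For LPF the definition calls for a value that the schedule does not collect. For ETF the schedule collects a value that the definition does not place.

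The children affected are treatment failures, so whatever is missing or taken at a different time is related to response to the drug. An analysis plan can choose among readings that exist, but it cannot supply one that was never taken on the rescue day. That is why the matter belongs in the protocol.

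**Working it through.** **Step 1. Set the two rules side by side.**

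| Class | Second value required by the outcome | Second value scheduled | Match |
|---|---|---|---|
| No failure (ACPR) | Day 42 | Day 42 | Yes |
| LCF | Day of rescue therapy | Time of clinical failure | Yes, if rescue starts on the day of failure |
| LPF first found on day 42 | Day of rescue therapy | Day 42 | Yes, if rescue starts that day |
| LPF found before day 42 | Day of rescue therapy | Day 42 only | No |
| ETF | Not named; read literally, day 42 | Time of clinical failure | No |

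**Step 2. Look for another source of the LPF reading.** The hemoglobin paragraph under Laboratory studies names the device but no days. The adverse-event section grades hemoglobin results but schedules no measurement. The selection criteria cover day 0. The follow-up schedule is therefore the only text that times re-measurement, and the fingerpricks it lists at other visits are for smears and filter paper.

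**Step 3. Ask whether the schedule could be meant to include LPF.** It spells out its classes in a bracket, and the protocol's own definition of clinical treatment failure also leaves LPF out. Staff following the text would not take the reading.

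**Step 4. Bound the number of children.** No figure is attached to the hemoglobin outcome, so there is none to reproduce. The scale comes from the sample-size section:

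- Expected failures: 0.075 × 300 = 22.5, in line with the stated 22.
- Ceiling, if every failure were LPF: 22 / 300 = 7.3%.
- If one third are LPF (assumption): 22 / 3 ≈ 7 children; 7 / 300 = 2.3%.
- If one half are LPF (assumption): 22 / 2 = 11 children; 11 / 300 = 3.7%.

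The protocol gives no LPF share. The ceiling reads the 7.5% as covering all three failure classes. Any LPF first found on day 42 should be subtracted from these counts.

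**Step 5. Scale of the effect on the mean, for illustration only.** If the affected children were left out and their mean change differed from the others' by an assumed 1 g/dL, the overall mean would shift by (22 / 300) × 1 ≈ 0.07 g/dL at the ceiling. With 7 to 11 children the shift is (7 / 300) × 1 ≈ 0.02 to (11 / 300) × 1 ≈ 0.04 g/dL. The sign depends on how these children's hemoglobin behaves, on which the protocol gives no data.

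**The case against.** The strongest reply is that the consequence is small and easily overstated. Much of that is right.

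- **A reader might infer that LPF children have no follow-up hemoglobin at all.** The text does not support this. The schedule keeps a day-42 measurement, and a child with LPF has had no clinical failure, so that measurement applies. An LPF first found on day 42 has a reading that day. One found earlier may have a later day-42 reading if still followed, though the protocol does not say whether follow-up continues after rescue. What is missing is the rescue-day value.
- **A reader might infer that ETF readings are wasted.** That is not established either. Hemoglobin results are graded for adverse events, so a failure-day reading has a stated safety use. Leaving ETF out of the outcome may be deliberate, since an early reading says little about recovery. What stands is an ambiguity: the outcome does not say how these children enter it.
- **A reader might infer that mean recovery is biased upward.** The document gives no basis for a direction. It also leaves open whether the affected children would be dropped or measured after rescue, and these are different problems.
- **The outcome is not uncomputable as a whole.** It can be computed for children without failure, and for LCF when rescue starts at failure.
- **Little else depends on it.** All children receive DP, so no treatment comparison is distorted. Neither the pharmacokinetic primary outcome nor the sample-size argument uses hemoglobin.

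These points narrow the consequence and lower the severity. They do not remove the mismatch: the definition explicitly asks for a rescue-day value in LPF, and nothing schedules it.

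**Conclusion.** The two sections contradict each other and must be reconciled. As written, the hemoglobin outcome cannot be computed as defined for children with LPF detected before day 42, and the place of the ETF value is unstated. The absent or mistimed values are tied to treatment outcome.

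The conclusion rests on the text alone and needs no assumption. Its size does need assumptions. Taking the 22 expected failures as all classes together, at most about 7% of 300 children are affected; if a third to a half are LPF, it is 7 to 11 children, or roughly 2 to 4%. The direction and size of any bias cannot be derived from the document.

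Severity is minor to moderate: one descriptive secondary outcome in a small share of children, but a reading that cannot be recovered once the visit has passed.

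**What to change.** 1. In the Follow-up schedule, add a hemoglobin reading on the day of rescue therapy for children classified as LPF, so that the schedule delivers what the outcome asks for.
2. In the secondary outcome, state how ETF children are handled: either their failure-day value is used, or they are left out on purpose with the reason given. The text compels neither choice.
3. Use the same failure classes and the same measurement day in both sections. At present one refers to the day of rescue and the other to the time of failure.

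Whether to report change to day 42 separately from change to the rescue day can be left to the analysis plan.

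The cost is matching wording in two places and, on the assumed LPF share, about 7 to 11 extra portable readings (22 at the ceiling). They can use blood from the fingerprick already taken for the smear when rescue starts at the visit where parasites are found. No dose or treatment rule is touched.

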### *4. Assessment of adverse events*

### Definition

### An adverse event is defined as "any untoward medical occurrence in a patient or clinical investigation subject administered a pharmaceutical product that does not necessarily have a causal relationship with this treatment." (ICH Guidelines E2A). An adverse event can further be broadly defined as ANY untoward deviation from baseline health which includes:

### Worsening of conditions present at the onset of the study

### Deterioration due to the primary disease

### Intercurrent illness

### Events related or possibly related to concomitant medications

### (International Centers for Tropical Disease Research Network Investigator Manual, Monitoring and Reporting Adverse Events, 2003).

### A serious adverse event is defined as an experience that results in any of the following outcomes:

### Death during the period of study follow-up

### Life-threatening experience (one that puts a patient at immediate risk of death at the time of the event)

### Inpatient hospitalization during the period of study follow-up

### Persistent or significant disability or incapacity

### Specific medical or surgical intervention to prevent one of the other serious outcomes listed in the definition.

### Identification of adverse events:

At each follow-up visit (days 1, 2, 3, 4, 5, 7, 14, 21, 28, 35, and 42 and any unscheduled day, study clinicians will assess patients according to a standardized clinical record form. A severity grading scale, based on toxicity grading scales developed by the WHO and the National Institutes of Health, Division of Microbiology and Infectious Diseases, will be used to grade severity of all symptoms, physical exam findings, and hemoglobin results. Any new event, or any event present at baseline that is increasing in severity, will be considered an adverse event.

Reporting of adverse events:

For each possible adverse event identified and graded as moderate, severe or life threatening, an adverse event report form will be completed. An adverse event report form will not be completed for events classified as mild, as these symptoms are common and difficult to distinguish from signs and symptoms due to malaria. The following information will be recorded for all adverse experiences that are reported:

1. Description of event
2. Date of event onset
3. Date event reported
4. Maximum severity of the event
5. Maximum suspected relationship of the event to study medication
6. Is the event serious?
7. Initials of the person reporting the event
8. Was the event episodic or intermittent in nature?
9. Outcome
10. Date event resolved

Reporting of serious adverse events and protocol deviations

The IRSS core facility staff will be responsible for notifying the IRBs that a serious adverse event has occurred. All serious events shall be reported to the UCSF Committee of Human Research (CHR) within 10 days of the onset of the event. A UCSF AE report form (one for each event) shall be completed and faxed to the CHR. Any protocol deviations or problems involving study conduct or patient participation shall be reported in a similar manner, following IRB procedures.

Management of serious adverse events

For all SAEs, the relationship of the events to the study medication shall be determined by the clinicians. If a patient experiences an SAE while receiving treatment for uncomplicated malaria with their assigned study treatment, the study medication will be stopped if the SAE is felt to be probably or definitely related to the study medication and the patient will be treated with quinine. Plans for additional follow-up, including laboratory tests, will be individualized to each subject as appropriate for the clinical setting. If an SAE occurs while a patient is not receiving treatment with study medications, treatment and plans for follow up will be individualized as appropriate for the clinical setting.

**RECRUITMENT &TREATMENT PROCEDURES**

## *Study sites*

The study will be conducted in Bobo-Dioulasso, the second main city of the country. The patients will be recruited in 3 public dispensaries for children (Colsama, Ouezzin-Ville, Sarfalao)

1. ***Recruitment & selection criteria***

Study subjects will be recruited from the public health facilities. Patients who present with symptoms suggestive of malaria (fever or history of fever) will be referred to the outpatient laboratory for a fingerprick for screening thick blood smear (using standard Giemsa staining). Thick blood slides will be read and counted by the laboratory technicians. The parasite density of positive screening thick blood smears will be estimated by counting the number of asexual parasites per 200 leukocytes, assuming a leukocyte count of 8,000/l. At the time of screening, study personnel will record basic information including patient age, gender, axillary temperature and date. All patients who have a positive screening thick smear with a parasite density of 2000-200,000/ul will be referred to the study clinician for further evaluation. If the patient satisfies the selection criteria, he/she will be enrolled in the study and referred to the study nurse for treatment administration. All patients who do not satisfy the initial selection criteria and are excluded from study enrolment will be referred back to the outpatient department for appropriate care.

## Selection criteria

On day 0, patients with symptoms suggestive of malaria and a positive screening thick blood smear will be assessed for the following selection criteria by study physicians:

1. Not previously enrolled in this study
2. Age > 6 months
3. Weight > 5 kg
4. Fever (> 37.5ºC axillary) or history of fever in the previous 24 hours
5. Absence of any history of serious side effects to study medications
6. No evidence of a concomitant febrile illness in addition to malaria
7. Provision of informed consent and ability to participate in 42-day follow-up (patient has easy access to health unit)
8. No history of antimalarial use in the previous two weeks
9. No danger signs or evidence of severe malaria defined as:

- Unarousable coma (if after convulsion, > 30 min)
- Recent febrile convulsions (within 24 h)
- Altered consciousness (confusion, delirium, psychosis, coma)
- Lethargy
- Unable to drink or breast feed
- Vomiting everything
- Unable to stand/sit due to weakness
- Severe anemia (Hb < 5.0 gm/dL)
- Respiratory distress (labored breathing at rest)
- Jaundice

Patients fulfilling these criteria will be assigned a study number and will be referred to the laboratory. A second fingerprick blood sample will be obtained to prepare thick and thin blood smears, collect blood on filter paper, and for measurement of hemoglobin. Patients with hemoglobin levels < 5.0 gm/dL will be excluded after enrollment based on criteria for severe malaria (see above) and immediately referred back to the study physicians for appropriate care. After going to the laboratory, the subjects will be referred to the study nurse for treatment allocation and treatment with the study medications. Patients must also meet the following criterion:

1. Absence of repeated vomiting of study medications on day 0

Results of the Giemsa-stained thick and thin blood smears obtained on day 0 will not be available until after the patients have been treated and discharged from the clinic. Patients will return to the clinic on day 1 and will be excluded from the study if the following inclusion criteria are not met:

1. *P. falciparum* mono-infection
2. Parasite density 2000-200,000/ul
3. ***Treatment administration***

Administration of medications will be performed by the study nurse who will record the date and time of treatment and the patient's study number.

Administration of all study drugs will be directly observed. If a patient fails to return to the clinic he/she will be visited at home by a home visitor who will collect information on where patients live. If patients miss their second dose of study drug, they will be excluded from the study. Study drugs given to young children will be crushed, mixed with water, and administered as slurry. Study drugs administered to older children will be given as tablets or fractions of tablets to be taken orally with a glass of water. Patients will be observed for 30 minutes to ensure that the medications are not vomited. Any patient who vomits the medication within 30 minutes of administration will be retreated with a second dose. Any patient who vomits repeatedly (> 3 times) will be excluded and referred for treatment with parenteral quinine.

